## Intervention

### Weight-loss information for all participants

Participants will be presented with a psycho-educational component common to all intervention conditions followed by, if assigned to the intervention conditions, the behaviour change components based on the HAPA. The components will be delivered by an interactive video presentation by an investigator. Table 1 outlines the components specific to each of the three study conditions.

The significance of adopting theory-based intervention techniques delivered by video means that the intervention is evidence-based, cost effective, requires minimal contact with the participant, provides flexibility for delivery, and is easily available. The video presentation allows messages to be conveyed in a consistent manner and reduces experimenter bias and provides greater control over potential variation in delivery across participants. All participants will receive identical content in relation to study design, psycho-education information, dietary intake and physical activity guidelines. Thus differences between the control and intervention conditions can be attributed purely to the intervention components. The participants in the two intervention conditions will receive the same information regarding the mental imagery and implementation intentions instructions, and thus differences in these intervention conditions can be attributed to the goal reminder text messages and not differences in intervention delivery style.

The main components of the video presentation are outlined below^a^. The pre-recorded video presentation provided to participants within all conditions, will introduce participants to study information and basic concepts of weight loss including psycho-education. The participants will be informed that they will be required to adhere to two guidelines for physical activity and dietary intake, respectively, in accordance with the weight-loss intervention.

The physical activity guideline encourages participants to exercise and be physically active. Participants will be instructed to “*engage in physical activity and be as active as possible. Engage in a minimum of 30 minutes of planned daily exercise*” in accordance with the Australian physical activity guidelines [39]. Participants will be provided with examples of physical activity and exercise, and be informed that more intensive exercise will assist them in reaching their *weight-loss* goal. Participants will be instructed to record some goals related to the physical activity guidelines.

The dietary intake guideline encourages participants to monitor their energy intake. The participants are instructed: “*monitor your energy intake and ensure your calorie (or kilojoule) intake amount is somewhere in-between the minimum and maximum allowance”.* Each participant will be provided with an individually recommended daily calorie intake amount needed for weight-loss. The Katch-McArdle Formula will be used to calculate the minimum amount of energy needed for one’s body to function, or the calories needed to maintain ones weight, referred to as basal metabolic rate (BMR), [40]. The Katch-McArdle formula takes into consideration an individual’s lean body mass. (BMR = 370 + (21.6 × lean mass in kg). Total daily energy expenditure is calculated by multiplying the BMR to a number representing the individual’s physical activity level. The outcome is subtracted by 500 calories to provide individuals with the recommended number of calories needed to consume to achieve weight-loss [10]. Participants’ calorie intake allowance will be recalculated at week 6 to account for body weight changes. To assist in meeting their daily recommended calories allowance, participants will be provided with information on the definition of a calorie, information on calories versus kilojoules, how to calorie count, how to use a calorie counting book, suggestions on food and drink consumption to assist in remaining within a participant’s daily calorie allowance, how to ensure a healthy diet including information on the Australian dietary guidelines [41], and examples of healthy eating. Participants will be instructed to record some goals related to the dietary intake guidelines.

### Components for intervention conditions

The pre-recorded video presentation provided to participants in the intervention conditions will also include the mental imagery and implementation intentions intervention components. Participants will be asked to create implementation intention plans using an if-then format [20]. Participants will be provided with instructions to guide them to mentally imagine the steps needed to reach their goals, and the goal outcome. Participants will be directed to record their goals, if-then plans, and mental imagery steps. Information on the development of the behaviour-change intervention components based on the HAPA is outlined below.

Research has highlighted the importance of outlining details of the behaviour change techniques used in behavioural interventions in relation to how they fit the theory [18,33,42,43]. This allows for an understanding of the content that an intervention uses, the methods, and the ‘active ingredients’ that lead to behaviour change. Michie and Prestwich [44] also highlight the importance of not only using theory to guide an intervention, but also identifying the theory components that relate to the intervention techniques.

Table 2 provides details of our systematic method of matching the study techniques with the theoretical components; this allows for better understanding of how the theory informs the intervention design and assists in evaluating the intervention effectiveness and theory [42,44]. The table includes the behavioural objective or target behaviour to be changed such as the diet or physical activity guideline, the theory-based psychological concept employed, the behaviour change technique within the theoretical framework that relates to the objective, the strategies that will be used in the present study linking the performance objective and behaviour change technique, and the evaluation method, such as the questionnaires or tools that will be used to evaluate whether the strategies employed resulted in changes in the theoretical construct to which it pertained.

**Table 2 Tab2:** **Systematic process matching behaviour-change technique with theoretical components for the HEALTHI program**

**Objective/Behaviour**	**Psychological variable targeted**	**Behaviour change technique (theoretical framework)**	**Implementation strategies**	**Evaluation**
1. Diet: *Monitor your energy intake and ensure your calorie (or kilojoule) intake amount is somewhere in-between the minimum and maximum allowance amount.*	Risk perception	Information provision.	Provide information on obesity related health factors.	Questionnaire items measuring Risk perception.
	Planning	Implementation Intentions	Participants create If-then plans on: how they plan to count calories, and how to keep calories to a minimum.	Questionnaire items measuring planning and level of If-then plan.
	Self-efficacy and motivation	Mental Imagery	Participants are directed to imagine the steps needed to reach their If-then plan.	Questionnaire items to measure self-efficacy and motivation.
			For example, imagining that they want to have a fatty food, and then imagine the steps required to implement their implementation intentions that target this obstacle.	
2. Physical Activity: *Engage in physical activity and be as active as possible. Engage in a minimum of 30 minutes of planned daily exercise.*	Risk perception	Information provision	Provide information on obesity related health issues and benefit of physical activity.	Questionnaire items to measure risk perception.
	Planning	Implementation Intentions	Participants create If-then plans on how they will engage in exercise, and what exercise they will perform.	Questionnaire items to measure planning and level of the If-then plan.
	Self-efficacy and motivation	Mental Imagery	Participants are directed to imagine the steps needed to reach their If-then plan.	Questionnaire items to measure self-efficacy and motivation.
*Information on objectives needed for both Goal 1 (dietary intake) and Goal 2 (physical activity)*	Evaluation	Self-evaluation	Self-monitor dietary intake and physical activity involvement.	Food, drink, and exercise diary.
				Questionnaires to measure dietary and physical activity behaviour.
				Body weight measurements.
	Outcome expectancies (subjective beliefs about unforseen events of a person’s behaviour with succeeding outcomes. That is, a person’s expectations about the consequences of an action).	Information provision.	When changing behaviour, the outcomes are viewed as being negative or positive (e.g., weight-loss) and this influences intention to engage in target behaviour (exercise, diet).	Questionnaire items to measure outcome expectancy.
			Information on positive outcomes of weight-loss and engaging in diet and exercise.	

Delivery mode = intervention delivered via online Qualtrics™ with incorporated video presentation.

One condition will receive goal reminder text messages.

Intensity time = participants are asked to view the intervention once and complete the various activities incorporated within the intervention.

Setting = Clinic room within Curtin University.

For example, the objective *“*monitor your energy intake to ensure your calorie (or kilojoule) intake is somewhere in-between the minimum and maximum allowance amount” is listed as the behavioural objective or behaviour needed to be changed (Table 2). The intervention components are based on theory-based psychological concepts: risk perception and planning. The planning variable target is matched with the behaviour change techniques of implementation intentions. The implementation intentions relate to the use of the strategy of directing participants to create if-then plans in relation to the diet guideline. The strategy will be evaluated by having participant’s complete self-reported questionnaires on planning and the if-then plan will be evaluated by the researcher.

#### Text message intervention component

Participants in the intervention with text message condition, will receive a text message once a week for a total of twelve weeks. The text message content will include goal reminders that relate to the participant’s diet and physical activity goals, implementation intentions and mental imagery that were set at baseline. For example: “Hello. I would like to ask you to take the time to review and remember your goals and the steps you need to take to reach them. Try and remember (or refer to your HEALTHI Program handouts) when you imagined the steps for your dietary intake and physical activity/exercise goals when watching the video? Take a few minutes to imagine these steps to reach your goals so it is clear in your mind”.

## Assessments

Multiple measures of biomedical, psychological, and behavioural outcomes and measures will be used to assess the intervention effectiveness; these are discussed below.

### Biomedical outcomes

Key outcome biomedical outcome measures will be taken to monitor changes in cardiovascular disease risk and body weight and composition as a result of the intervention [7,9,45]. All the biomedical outcome measures will be conducted at baseline, 6 and 12 week periods unless specified otherwise.

Within a three day period prior to the clinic appointment, blood lipoproteins including low-density lipoprotein (LDL), high-density lipoprotein (HDL), total cholesterol (TC), triglycerides (TG), and blood glucose and insulin levels will be taken at an approved pathology laboratory using a venous blood sample from each participants.

*Body weight (kg)* will be recorded with participants wearing light clothing and no shoes, using a digital body composition monitor scale (Omron, model HBF 362). *Height* (cm) will be measured at baseline, to the nearest 0.1 cm using a stadiometer with participants wearing light clothing and no shoes. *Body mass index* (BMI) will be calculated using both the weight and height measurements using the formula weight in kilograms divided by the square of the height in meters (kg/m^2^). *Waist-hip ratio* (cm) will be calculated by measuring waist circumference in standing position at the narrowest area between the iliac crest and lateral lower rib, and hip measurement from the largest circumference of the lower abdomen. This will be measured to the nearest 0.1 cm using a circumference measuring tape (Seca 203). To ensure greater accuracy the measure will be taken twice and the average of the two readings will be used.

*Systolic blood pressure* (SBP) and *diastolic blood pressure* (DBP) will be measured using an automated, blood pressure monitor (A & D Medical, model UA-851) with participants in a supine position with the tested arm at the level of their heart for at least a minimum of 10 minutes before and during measurements [46]. The measure will be taken three times and the average reading will be used. Body composition including *bone mass, body fat percentage,* and *muscle mass* will be measured using the whole body dual-energy X-ray absorptiometry (DEXA, Lunar Prodigy; Lunar, Madison, WI, USA). Participants will be required to lie on a bed during the DEXA scanning with no jewellery or metal clothing. DEXA scans will be performed at baseline and 12 weeks. The dual-energy X-ray absorptiometry machine will be calibrated and a phantom scan undertaken daily.

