**Methods/Design:**

Overweight or obese participants will be randomly allocated to one of three conditions: (1) a psycho-education plus an implementation intentions and mental imagery condition; (2) a psycho-education plus an implementation intentions and mental imagery condition with text messages; or (3) a psycho-education control condition. The intervention will be delivered via video presentation to increase the intervention’s applicability in multiple contexts and keep costs low. We hypothesise that the intervention conditions will lead to statistically-significant changes in the primary and secondary outcome variables measured at 6 and 12 weeks post-intervention relative to the psycho-education control condition after controlling for baseline values. The primary outcome variable will be body weight and secondary outcome variables will be biomedical (body mass, body fat percentage, muscle mass, waist-hip circumference ratio, systolic and diastolic blood pressure, low-density lipoprotein, high-density lipoprotein, total cholesterol, triglycerides, blood glucose and insulin levels), psychological (quality of life, motivation, risk perception, outcome expectancy, intention, action self-efficacy, maintenance self-efficacy, goal setting and planning), and behavioural (self-reported diet intake, and physical activity involvement) measures. We also expect the intervention condition augmented with text messages to lead to statistically significant differences in the primary and secondary outcome variables at the follow up periods after controlling for baseline values.

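### The hip girth in the waist-hip ratio is placed on the lower abdomen, so the outcome as written is a ratio of two abdominal girths

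*Protocol article*

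**What the plan says.** The Abstract (Methods/Design) makes body weight the primary outcome and lists the "waist-hip circumference ratio" among the secondary biomedical outcomes. The Discussion names waist-hip circumference again as an example of the key biomedical outcomes.

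The only measurement rule is in Assessments, Biomedical outcomes. The numerator comes from "measuring waist circumference in standing position at the narrowest area between the iliac crest and lateral lower rib". The denominator is the "hip measurement from the largest circumference of the lower abdomen". The same paragraph fixes the tape model, a precision of 0.1 cm and duplicate readings: "the measure will be taken twice and the average of the two readings will be used". On timing, "All the biomedical outcome measures will be conducted at baseline, 6 and 12 week periods unless specified otherwise", and no exception is made for this ratio. It is therefore due at baseline, 6 and 12 weeks.

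Under Statistical analysis, the biomedical outcomes form one MANCOVA set with baseline values as covariates, followed by univariate ANCOVAs. The secondary biomedical outcomes are also dependent variables in the mediation models.

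**The concern.** A waist-hip ratio sets abdominal girth against the girth of the hips. The written landmark puts the denominator on the abdomen as well. In a sample with BMI between 25 and 40, the largest lower-abdominal girth is itself likely to reflect central fat. The denominator may then shrink with the very change that the numerator is meant to show.

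This is not detail that a condensed article leaves to a fuller protocol. The article states a landmark, in a paragraph specific enough for an assessor to follow, and the landmark does not match the outcome's name.

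At stake is one secondary outcome, but one with little backup. Among the outcomes listed in the Abstract it is the only one aimed at where fat is carried. The DEXA outputs are bone mass, body fat percentage and muscle mass, and DEXA is done only at baseline and 12 weeks. Waist circumference is measured but not listed as an outcome in its own right.

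**Working it through.** **Step 1: the text.** The places in the article that mention the measure compare as follows.

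| Place | What it gives |
|---|---|
| Abstract, Methods/Design | Name of the outcome only |
| Procedure | That it is taken at clinic appointments |
| Biomedical outcomes | Waist site; hip site on the lower abdomen |
| Discussion | Name only |

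One section gives a landmark and none corrects it. The literal outcome is therefore (narrowest girth between iliac crest and lower rib) / (largest lower-abdominal girth).

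**Step 2: what this could do to the signal.** The article has no figure to reproduce, so all girths below are assumptions. Let the waist be W and fall by dW, and let the denominator be H and fall by dH. Then

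relative change in ratio = [(W - dW)/(H - dH)] / (W/H) - 1.

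Take W = 100 cm and dW = 5 cm:

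| dH as share of dW | H = 102 cm | H = 108 cm | H = 112 cm |
|---|---|---|---|
| 0 | -5.00% | -5.00% | -5.00% |
| 0.50 | -2.61% | -2.75% | -2.83% |
| 0.75 | -1.37% | -1.58% | -1.71% |
| 1.00 | -0.10% | -0.39% | -0.56% |

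Worked cell, H = 108 and dH = 2.5: before, 100/108 = 0.926; after, 95/105.5 = 0.900; change -2.75%.

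The rows matter far more than the columns. The result depends mainly on how much the denominator shrinks, and much less on its starting size.

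**Step 3: does the site alone cause the loss of signal?** Let the waist fall from 105 to 100 cm, and assume a buttock girth of 115 cm and a lower-abdominal girth of 110 cm.

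| Assumed loss | Buttock denominator | Lower-abdominal denominator |
|---|---|---|
| 3 cm at both sites | (100/112)/(105/115) - 1 = -2.2% | (100/107)/(105/110) - 1 = -2.1% |
| 5 cm at both sites | (100/110)/(105/115) - 1 = -0.4% | (100/105)/(105/110) - 1 = -0.2% |

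With equal losses the two sites give nearly the same answer. They separate only if the lower abdomen loses more than the buttocks: 3 cm at the buttocks gives -2.2%, and 5 cm at the lower abdomen gives -0.2%. A 6 cm loss at the lower abdomen gives (100/104)/(105/110) - 1 = +0.7%, a rise despite the smaller waist. Unequal loss is plausible, but nothing in the document establishes it or its size.

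**The case against.** The strongest reply is that this is loose wording. The sentence does say hip, it looks for a largest girth after a waist taken at a narrowest one, and a horizontal tape at pelvic level goes round the buttocks too. Staff may be taking an ordinary hip girth. That possibility stands, but it does not remove the point: neither a reader nor a new assessor can tell from the text, and the text read plainly gives the wrong site.

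A second reply is that the consequences are limited, and this stands in full. The same rule applies to every arm and visit, the comparison adjusts for baseline, and body weight is untouched. No comparison with external waist-hip norms is planned, so the lack of comparability harms interpretation rather than any stated test. The centimetre label on a ratio is a clerical slip. Not listing waist circumference separately is a design choice, not an error.

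A reader might infer something stronger: that the ratio will hardly move when abdominal fat is lost, or will keep only about a tenth of its signal. The document does not support that. Such a figure comes from assuming a larger loss at the lower abdomen than at the buttocks, and with equal losses the contrast nearly vanishes. Insensitivity when both girths shrink together is a property of any waist-hip ratio.

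**Conclusion.** The stated hip landmark is wrong for the outcome it defines. This rests on the text alone and needs no assumed figure. Followed literally, the result is not a waist-hip ratio and should not be reported or compared as one.

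Weaker response to loss of central fat is the plausible direction. It rests on the assumption that the lower abdomen shrinks more than the buttocks, and its size cannot be derived. For a 5 cm waist loss, the assumed girths in the first table give anything from -5.0% to -0.1%.

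The expected harm is lost validity and sensitivity in one secondary outcome and in the biomedical analyses that use it. It is not bias between arms, provided the same site is used for all participants at all visits. The primary outcome is unaffected. The point is worth correcting because the correction is nearly free.

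**What to change.** - Restate the hip landmark in Biomedical outcomes as the largest circumference over the buttocks, and drop the unit from the ratio.
- Confirm which site staff actually use, and keep it the same at baseline, 6 and 12 weeks.
- Report waist circumference (cm) as a supplementary outcome.

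If participants have already been measured at the lower abdomen, keep that site for them so that their follow-up values remain comparable with baseline. Report the ratio with its actual landmark stated, not as a standard waist-hip ratio, and give waist circumference alongside it. Waist should not take the ratio's place, because that would swap out a prespecified outcome during the trial.

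The cost is one line in the measurement procedure and one in the outcome list, with no new visit or equipment. The small downside is one more secondary outcome.

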Participants will need to provide written consent prior to participation. Prior to each clinic appointment participants will complete questionnaires measuring baseline psychological and behavioural outcomes including a 3 day food, drink, and exercise diary. Within a three day period, prior to their clinic appointment, participants will be required to attend to a pathology clinic to take blood sample measures. Furthermore, at each clinic appointment participants will engage in baseline biomedical assessments: blood pressure, weight, waist-hip ratio, and at baseline and week 12 body composition measures. At the first clinic appointment participants will be asked to view a pre-recorded video presentation that contains the intervention information, followed by the completion of a questionnaire containing the post-intervention measures. One of two video presentations will be provided to participants, one designed for the control condition participants, and the other for the two intervention conditions. The duration of the video presentation is approximately 60 and 76 minutes for the control and intervention conditions respectively. Due to the pauses in the video to complete various activities and the break time the intervention manipulation duration may last approximately 90 to 120 for the control condition, and 150 to 210 for the intervention conditions. In addition, participants allocated to the intervention with text message condition will receive goal reminder text messages over the 12 weeks of the intervention. Prior to leaving the clinic, all participants will be provided with their future appointment times and a set of tools to assist them with monitoring their physical activity and calorie intake: A copy of the Calorie King™ book [36], Calorie Counter diary [37], the Australian dietary guidelines [38], and Australian physical activity guidelines [39]. Participants will be encouraged to contact the researcher if any queries arise. In addition, a personalised email providing a handout of the essential program information such as the guidelines and the participant’s responses to various activities (including goals) when watching the video presentation will be sent to the participant via email. The participant responses to the activities will be assessed by the research team to ensure program compliance.

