#### Statistical analysis

A series of 3 (condition: control, intervention, and intervention with text message) × 2 (time: 6 and 12 weeks) mixed model multivariate analyses of covariance (MANCOVAs) with time as a repeated measures variable will be used examine the effects of the intention over time on study outcome variables. Baseline measures will be covariates in the model. A separate MANCOVA will be conducted for each set of dependent outcome variables: biomedical, behavioural and psychological. Pending significant multivariate effects, follow-up univariate analysis of covariance (ANCOVAs) will be used to identify differences for individual variables within each outcome set. Post-hoc follow-up tests will also be conducted to locate individual differences at the time intervals. Mediation analyses will be conducted by mediated multiple linear regression analysis with dummy-coded intervention conditions as the independent predictor variables, the constructs from the HAPA included as mediating variables, and the primary and secondary biomedical outcome variables as the dependent variables. Mediation will be confirmed through significant bootstrapped indirect effects using Preacher and Hayes’ [56] algorithms for multiple mediation and the PROCESS macro. Missing data will be handled by multiple imputation using regression analysis with the Markov-chain Monte Carlo (MCMC) estimation method. In addition, we will adopt a full intention-to-treat analysis with last measured data points carried forward in order to provide a conservative estimate of the effects.

Sample size has been determined by a power analysis using the G*Power 3.1 Program, suitable to evaluate differences between the three condition levels greater than 10%, with statistical power set at > 0.80 and alpha set at *p* < .05 [57]. A large effect size is assumed as previous studies that have used implementation intentions and reminder text messages [31], as well as studies using mental imagery and implementation intentions to increase exercise behaviour [58], have found large effect sizes. Given the estimated effect size, the total sample size required post-test is 66 and considering a potential 35% drop out rate and eliminations of cases due to missing data or spoilt questionnaires based on previous trials [21], we plan to recruit 102 participants at baseline or until the required sample size has been achieved.

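### The DEXA outcomes have no week-6 value, yet the biomedical MANCOVA uses weeks 6 and 12 as its repeated factor and makes no exception for them

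*Protocol article*

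**What the plan says.** **Schedule.** The Biomedical outcomes section says that bone mass, body fat percentage and muscle mass "will be measured using the whole body dual-energy X-ray absorptiometry", and that "DEXA scans will be performed at baseline and 12 weeks". The Procedure section agrees. Its list of clinic assessments reads "blood pressure, weight, waist-hip ratio, and at baseline and week 12 body composition measures".

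**Status of the variables.** The abstract's Methods/Design paragraph says "secondary outcome variables will be biomedical (body mass, body fat percentage, muscle mass, waist-hip circumference ratio" and continues with other laboratory and clinical measures. Bone mass is not in that list but is named among the DEXA measures in the Biomedical outcomes section. The same abstract paragraph frames the hypotheses as "changes in the primary and secondary outcome variables measured at 6 and 12 weeks post-intervention".

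**Analysis.** The Statistical analysis section specifies three conditions crossed with "2 (time: 6 and 12 weeks) mixed model multivariate analyses of covariance (MANCOVAs) with time as a repeated measures variable". It adds: "Baseline measures will be covariates in the model". There is one such model for each of the biomedical, behavioural and psychological sets. Univariate ANCOVAs follow only if the multivariate effect is significant. Missing data are to be multiply imputed by regression with MCMC. An additional intention-to-treat analysis carries the last measurement forward and is described as conservative.

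**The concern.** Baseline is a covariate, so the only levels of the time factor are weeks 6 and 12. A DEXA variable supplies one of these two levels. The other is absent for everyone by design, in all three arms, and the analysis section does not set these variables aside.

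The problem may reach beyond two or three secondary outcomes. Body weight is described under Biomedical outcomes, no separate model for the primary outcome is given, and the univariate tests wait on the multivariate result for the set. If the set's multivariate test cannot be computed as specified, someone must decide during the analysis which variables make up the test that gates the primary outcome. That decision should be fixed in advance.

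**Working it through.** **1. The plan's own sample size.** This is reproduced first because the later figures use the same N. The protocol gives 66 participants post-test, power above 0.80, alpha 0.05, three arms, and an effect described only as large. Assume Cohen's f = 0.40 for large. For a one-way comparison of three arms, the noncentrality is λ = f² × N and the degrees of freedom are 2 and N − 3.

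- The smallest N with power of at least 0.80 is 64 (0.805), which rounds up to 66 for equal arms of 22.
- At N = 66, λ = 0.16 × 66 = 10.56 and power is 0.818.
- For dropout, 66 / (1 − 0.35) = 101.5, so 102.

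Both stated figures reproduce and neither is in dispute.

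**2. Schedule against model cells.**

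| Variable | Baseline (covariate) | Week 6 (time level 1) | Week 12 (time level 2) |
|---|---|---|---|
| Body weight, blood pressure, waist-hip ratio, blood measures | yes | yes | yes |
| Body fat %, muscle mass, bone mass (DEXA) | yes | none | yes |

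Week-6 DEXA is 100% missing by design. A MANCOVA on rows complete for the whole biomedical set would keep 0 of 66 participants.

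**3. Multiple imputation.** An imputation model for week-6 body fat needs some observed week-6 values to estimate their mean, their variance and their relation to arm and to the other visits. There are none. The imputed values would reflect modelling assumptions alone, so the week-6 arm effect is not identified.

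**4. Carry-forward.** Let b be the baseline value and y12 the week-12 value. Carry-forward sets y6 = b for everyone. With b as covariate:

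- Week 6: y6 is exactly b, so the adjusted arm difference is 0.
- Condition by time: y12 − y6 = y12 − b. Subtracting the covariate from the response changes only the slope on b. The arm coefficients, residuals and F statistic are those of the week-12 ANCOVA.
- Time average: (y6 + y12)/2 = (b + y12)/2. The arm coefficients and the residual SD are both half those of the week-12 ANCOVA, so F is again the same.

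A simulation agrees (4,000 trials, 22 per arm, assumed baseline to week-12 correlation 0.8, effect of 0.85 residual SD in both active arms):

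| | Week-12 ANCOVA | Time-averaged test | Condition by time |
|---|---|---|---|
| Rejection, no effect | 0.052 | 0.052 | 0.052 |
| Rejection, effect 0.85 SD | 0.811 | 0.811 | 0.811 |

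The mean time-averaged estimate was 0.43 SD, half of 0.85. The effect used corresponds to f = 0.85 × √(2/9) = 0.40.

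**5. How often an artificial interaction would be declared.** Suppose the true arm effect is the same at both visits, so that no interaction exists. The carried-forward interaction test then rejects as often as the week-12 ANCOVA does. With N = 66, one covariate and degrees of freedom 2 and 62:

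| Assumed f | λ = f² × 66 | Rejection rate |
|---|---|---|
| 0.25 | 4.125 | 0.41 |
| 0.40 | 10.56 | 0.82 (0.81 simulated) |
| 0.50 | 16.5 | 0.95 |

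**6. After the fix.** Week-12 ANCOVA at N = 66 and f = 0.40 has power 0.818, unchanged by the loss of one degree of freedom to the covariate.

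**The case against.** The strongest reply is that the schedule is openly disclosed. The Biomedical outcomes section allows for exceptions to the three-visit rule and then names DEXA as one, and the Procedure section agrees. An analyst would notice the empty cells at once, leave DEXA out, and run the model on the other variables. This is fair as to the schedule, which is sound. It does not repair the analysis section, which has no matching exception. Nor is this detail that an article can leave to a fuller plan, because the article states a specific model that its own schedule cannot feed.

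Four stronger readings are tempting and are not supported:

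- *Carry-forward produces false positives.* It does not create a treatment effect. With no effect, the rejection rate stays near 0.05. What goes wrong is the label and time pattern given to a real week-12 effect. The 0.82 is simply the week-12 power at an assumed f.
- *Halving the averaged effect loses power.* It does not, because the residual SD halves as well. The damage is to the size of the reported estimate.
- *The primary analysis has no data.* Zero complete cases would follow from listwise deletion, which the protocol does not specify. Body weight is measured at every visit. Its dependence on this MANCOVA is the natural reading, but the members of the biomedical set are not listed in the analysis section.
- *The abstract claims that every secondary outcome is measured at both visits.* Its wording is loose, but it does not say so.

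Two further replies fail. A likelihood-based mixed model tolerates some missing cells but cannot estimate a week-6 effect for a variable never observed then. The weighing scale is called a body composition monitor, but the protocol uses it for weight and assigns fat and muscle to DEXA.

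**Conclusion.** The point holds as a contradiction between the measurement schedule and the stated analysis. It needs no outside figure. The 3 × 2 biomedical MANCOVA cannot be fitted to observed data with the DEXA variables in it, and neither stated missing-data method supplies what is absent. The contradiction directly affects body fat percentage and muscle mass, and bone mass if it is analysed. It reaches body weight through the multivariate gate, on the natural reading of the set.

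Under carry-forward, the zero week-6 difference and the halved time-averaged estimate are exact. The frequency of a spurious interaction (about 0.41 to 0.95 for f from 0.25 to 0.50) rests on two assumptions: an effect size that the protocol does not give as a number, and a true effect equal at both visits. Type I error and power are not harmed.

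**What to change.** In the Statistical analysis section:

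- Take body fat percentage, muscle mass and bone mass out of the 3 × 2 biomedical MANCOVA, and list the variables that remain in it.
- Analyse each DEXA outcome by ANCOVA of the week-12 value on condition, adjusted for its own baseline value.
- State that week-6 DEXA values are neither imputed nor carried forward, because none were scheduled.

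In the outcome description, including the abstract, note that follow-up of the DEXA outcomes is at week 12 only.

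The cost is a few sentences. No scans are added, and the targets of 66 and 102 stand.
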